## Abstract

**Introduction:**

A quarter of breast cancers show human epidermal growth factor-2 (HER2) overexpression, where targeted therapy dramatically improves survival. However, cancer therapy-related cardiac dysfunction (CTRCD) occurs in up to 15% of patients. With the interruption of HER2 therapy, if necessary, and the initiation of heart failure therapy (HFT), HER2 CTRCD recovers in over 80% of cases. The need to continue HFT in ‘recovered’ HER2 CTRCD following completion of HER2 therapy is unclear and there are potential significant impacts on patient’s quality of life (QoL). The Randomised Controlled Trial for the Safety of Withdrawal of Pharmacological Treatment for Recovered HER2 Targeted Therapy Related Cardiac Dysfunction (HER-SAFE) aims to evaluate whether HFT can be safely withdrawn in non-high cardiovascular (CV) risk patients with ‘recovered’ HER2 CTRCD.

**Methods and analysis:**

This is a multicentre, open-label randomised controlled trial investigating whether withdrawal of HFT is non-inferior to continuation in non-high CV risk, breast cancer survivors with recovered HER2 CTRCD after cancer treatment completion. The primary endpoint is the incidence of guideline-defined cardiac dysfunction or clinical heart failure. Secondary endpoints include changes in cardiac blood biomarkers, cardiovascular magnetic resonance (CMR)-derived strain and tissue mapping and heart failure symptom questionnaires. The study will recruit 90 participants who will undergo serial clinical assessment over 12 months with advanced cardiovascular imaging (CMR scans with automated analysis at baseline, 6 and 12 months), cardiac biomarker measurement (six time points over 12 months), plus complete heart failure QoL and medication disutility questionnaires. This is the first multicentre study to address this significant clinical issue.

**Ethics and dissemination:**

This study was approved by the research ethics committee (London—London Bridge, 23/LO/0152). The results will be disseminated in peer-reviewed scientific journals.

**Trial registration number:**

NCT05880160.

STRENGTHS AND LIMITATIONS OF THIS STUDYThis is a multicentre study with participant cohort focused on HER2-targeted therapy-related cardiac dysfunction.Endpoint assessment using gold standard cardiovascular magnetic resonance (CMR) scans with artificial intelligence analysis for improved measurement precision.Unblinded study design, in keeping with other deprescribing trials.Cohort restricted to non-high cardiovascular risk patients; therefore, results will not be generalisable to higher risk populations.

## Introduction

### Human epidermal growth factor 2 (HER2+) breast cancer and HER2-targeted therapies

Breast cancer is the most common cancer worldwide, affecting more than 2 million people annually.^1^ More than 75% of patients now survive for 10 years or longer, with better life expectancy with early-stage disease.^2^ Overall, 15–20% of breast cancers overexpress the human epidermal growth factor 2 (HER2) gene and historically had poorer outcomes.^3 4^ HER2-targeted therapies dramatically improve survival,^5^,^7^ but are associated with acute, reversible cardiotoxicity.^8^,^10^ The overall reported incidence of symptomatic heart failure is 1.9%, while asymptomatic declines in left ventricular ejection fraction (LVEF) occur more commonly (approximately 15%), with higher rates when coadministered with anthracycline chemotherapy.^8 11 12^ This cardiotoxicity can lead to premature interruption or discontinuation of HER2 therapies, which is associated with worse cancer outcomes.^13 14^

### HER2-targeted therapy-related cardiac dysfunction

Unlike other cancer therapy-related cardiac dysfunction (CTRCD), HER2-targeted therapy-related cardiotoxicity is generally reversible on treatment discontinuation,^15^,^17^ and late cardiotoxicity is uncommon.^15 18^ For patients with early breast cancer, the duration of HER2-targeted therapy is 12 months and normalisation of cardiac function occurs in most patients; over 80% of patients with breast cancer and HER2 CTRCD show recovery at a median of 7 months post initial dysfunction.^15^ Myocyte apoptosis/necrosis is rare, and myocyte dysfunction is thought to be due to blockade of cardioprotective HER2 signalling and increased oxidative stress.^19 20^ The European Society of Cardiology (ESC) 2022 cardio-oncology guidelines recommend HER2-targeted therapies should be reviewed (with consideration to interrupting) for LVEF declines of >10% from baseline to <50%, with prompt initiation of heart failure treatments (HFTs), consisting of an ACE inhibitor (ACEi)/angiotensin receptor blocker (ARB) and/or a beta-blocker.^21^

There is, however, no evidence to guide the duration of this HFT in patients who have completed HER2-targeted therapy and whose cardiac function has ‘recovered’ (that is LVEF returned to >50%, the absence of cardiac symptoms and N-terminal pro-B-type natriuretic peptide (NTpro-BNP) in the normal range). The TRED-HF (Withdrawal of pharmacological treatment for heart failure in patients with recovered dilated cardiomyopath) study^22^ demonstrated that relapse was common in patients with recovered dilated cardiomyopathy (DCM) following HFT withdrawal, though the cohort and pathophysiology differ greatly, and the results may not be generalisable. As such, international society guidelines do not address the common clinical question of HFT continuation in recovered HER2 CTRCD.

### Evidence for medication withdrawal in recovered heart failure

Across general heart failure aetiologies, international guidelines recommend continuation of HFT indefinitely, even when cardiac function and natriuretic peptides normalise, to prevent relapse in cardiac dysfunction.^22 23^ Results from the TRED-HF study^22^ found a relapse rate of 44% over 6 months in patients with (predominantly idiopathic) DCM who underwent complete withdrawal of HFT, with zero relapse events in those continuing treatment. Cardiovascular magnetic resonance (CMR) imaging analysis from this study demonstrated that withdrawing therapy caused rapid adverse remodelling, with early tissue and functional changes, even among patients who did not relapse—notably an increase in left ventricular (LV) mass, cell mass, matrix mass and a reduction in global longitudinal strain (GLS).^24^ Other data have similarly found evidence of relapse on withdrawal of spironolactone in recovered DCM.^21^ This supports long-term prescription of HFT in patients with DCM, even for asymptomatic patients with normalisation of LVEF and biomarkers.

Patients in TRED-HF, however, differ from those with HER2 CTRCD, for whom LV impairment is generally reversible and where the cause is removed when cancer treatment completes. The risks of an ongoing pathophysiological process were high in TRED-HF with scar on CMR in 39% and truncating titin (TTN) gene mutations in 22%. Participants in TRED-HF had recovered from severe clinical heart failure (mean diagnosis LVEF 25%), atrial fibrillation in 24% and heart failure hospitalisation in 63%; whereas HER2 CTRCD is often detected during routine surveillance screening, in younger asymptomatic patients without pre-existing cardiovascular (CV) disease and with mild reductions in LVEF.^25^ High scar burden on CMR, higher B‐type natriuretic peptide level and lower LVEF at the initial LVEF recovery have been demonstrated as independent predictors of a relapse in cardiac dysfunction in patients with DCM^26^; factors that are again less common in patients with breast cancer and HER2 CTRCD.

### Medication disutility

An estimated 30 000 women under the age of 45 years will be diagnosed with breast cancer in the USA in 2024 and there are over 4 million living breast cancer survivors.^27^ Long-term, potentially life-long, compliance with HFT is challenging and can have significant impact on quality of life (QoL), especially in a younger cohort of patients where this may impact family planning.^28^ HFT is therefore commonly continued for at least 6 months post recovery, with subsequent individualised decision-making regarding stopping. This includes an assessment of concomitant comorbidities, CV risk factors, patient preference, level of physical activity and medication tolerance.^29^ This is, however, not evidence based, with no formal consensus recommendations to aid clinicians, hence practice varies widely.

Medication disutility (the inconvenience of taking a medication) is generally higher than recognised by clinicians—particularly in the preventative setting.^30^ It has been assessed formally for statins and bisphosphonates where patients on these medications would trade 4 or 6 months, respectively, of good health over 10 years to avoid taking them.^31^ The disutility of HFT has not been assessed. Formal exploration of patients’ perceptions of medication disutility in the setting of ‘recovered’ CTRCD has also not been performed, which implies that the impact of drug side effects and lifestyle choices on patient motivations are unclear.

## Methods and analysis

### Study design

This is a UK multicentre, open-label, randomised controlled trial to compare the phased withdrawal versus continuation of HFT for ‘recovered’ HER2 therapy-related cardiac dysfunction in patients with treated breast cancer at non-high CV risk.(figure 1).

**Figure 1 F1:**
[figure not shown]
Central illustration. Randomised Controlled Trial for the Safety of Withdrawal of Pharmacological Treatment for Recovered HER2 Targeted Therapy Related Cardiac Dysfunction (HER-SAFE). There is an evidence gap in the management of breast cancer survivors with recovered HER2-targeted therapy cardiac dysfunction that this study will address.

‘Recovery’ is defined as the absence of heart failure symptoms, with LVEF>50% for at least 6 months and NTpro-BNP<125 ng/L. CV risk is defined according to their cardiotoxicity risk status prior to HER2 therapy, as per the specific HER2-targeted therapies risk calculator from the Heart Failure Association and International Cardio-Oncology Society (HFA-ICOS) 2020 position paper on baseline cardiotoxicity risk assessment in patients with cancer; this is a risk score based on expert opinion, where the risk of future cardiotoxicity was considered as: low risk<2%, medium risk 2–9%, high risk 10–19% and very high risk≥20%.^25^
Table 1 describes the study as per the Consolidated Standards of Reporting Trials guidelines,^32^ and figure 2 illustrates the trial design.

**Table 1 T1:** ‘HER-SAFE’ extended Consolidated Standards of Reporting Trials guidelines items

	Description
Title	HER-SAFE: an open-label, randomised controlled trial to investigate the safety of withdrawal of pharmacological treatment for recovered human epidermal growth factor 2 (HER2)-targeted therapy-related cardiac dysfunction.
Trial design	Open-label, non-inferiority, randomised controlled trial.
Inclusion	Adult breast cancer with low or medium risk by baseline Heart Failure Association and International Cardio-Oncology Society (ICOS) cardiotoxicity assessment,^25^ who have completed HER2-targeted therapy, demonstrate recovered HER2-targeted therapy-related cardiac dysfunction (left ventricular ejection fraction>50% for 6 months, no heart failure symptoms and N-terminal pro-B-type natriuretic peptide and continued heart failure treatment since then (at least one of a beta-blocker and/or ACE inhibitor/angiotensin receptor blocker).
Exclusion	Ongoing cancer treatment for metastatic disease, life expectancy less than 12 months, anthracycline therapy-related cardiac dysfunction, any other known cardiomyopathy or the presence of another guideline-recommended indication to continue their heart failure medications.
Intervention	The phased withdrawal of pharmacological heart failure treatments.
Objective	To evaluate whether phased withdrawal of pharmacological heart failure therapy in patients with non-high cardiovascular risk breast cancer and ‘recovered’ HER2-targeted therapy-related cardiac dysfunction, after completion of cancer therapy, is non-inferior to continuation with regard to risk of recurrence in cardiac dysfunction.
Outcome	The incidence of relapsed cardiac dysfunction over 12 months, based on the ICOS 2021 guidelines^27^ definitions of cancer therapy-related cardiac dysfunction (CTRCD).
Randomisation	Minimisation using a biased coin probability method (70%) and marginal balance distance method. Minimisation factors are: current age over 65 years, baseline cardiovascular level greater than low,^4^ CTRCD severity greater than mild,^27^ cumulative anthracycline dose greater than 250 mg/m^2^ and any radiotherapy to the left breast.
Blinding	Unblinded.
Recruitment	Target: 90 participants. Power: 74 participants.
Recruitment	Open.
Registration	Clinicaltrials.gov: NCT05880160.London Bridge Research Ethics Committee (REF: 23/LO/0152).
Funding	British Heart Foundation (FS/CRTF/22/24395).

HER-SAFERandomised Controlled Trial for the Safety of Withdrawal of Pharmacological Treatment for Recovered HER2 Targeted Therapy Related Cardiac Dysfunction

**Figure 2 F2:**
[figure not shown]
Schematic of the Randomised Controlled Trial for the Safety of Withdrawal of Pharmacological Treatment for Recovered HER2 Targeted Therapy Related Cardiac Dysfunction (HER-SAFE). Following enrolment and baseline assessment, participants are randomised to withdrawal or continuation of their heart failure treatment and then followed up for 12 months.

### Study objectives

The primary objective of the study is to determine whether phased withdrawal of pharmacological HFT in patients with breast cancer and ‘recovered’ HER2-targeted therapy-related cardiac dysfunction, after completion of cancer therapy, is non-inferior to continuation with regard to risk of recurrence in cardiac dysfunction.

The secondary objectives of the study are to assess:

If relapse in cardiac dysfunction occurs, whether baseline CMR and biomarkers prior to treatment withdrawal predict subsequent relapse.How patient ratings of medication disutility depend on age, comorbidities, medication side effects and perceptions of disease severity.

### Participant selection

Participants who meet the required inclusion and exclusion criteria as shown in table 2 are eligible for enrolment into the study. Eligible participants will have completed HER2-targeted therapy as part of breast cancer treatment. Participants will be low or medium risk by baseline HFA-ICOS cardiotoxicity assessment.^25^ Participants will have been previously diagnosed and treated for HER2 CTRCD (meeting ESC guideline CTRCD definitions^33^), continued HFT since then (at least one of a beta-blocker and/or ACEi/ARB) and subsequently ‘recovered’. ‘Recovery’ of cardiac function is based on the prior definition^22^ of an LVEF of greater than 50% for 6 months (by echocardiography or CMR) and an NTpro-BNP within normal limits (125 ng/L).

**Table 2 T2:** Inclusion and exclusion criteria for ‘HER-SAFE’

Participant inclusion criteria	Participant exclusion criteria
Age>18 years old.	Any ongoing indications for HER2-targeted therapy.
Human epidermal growth factor 2 (HER2) positive, non-metastatic breast cancer.	Life expectancy<12 months.
Completion of HER2-targeted therapy.	High/very high baseline cardiovascular risk according to the Heart Failure Association and International Cardio-Oncology Society risk stratification.^25^
A prior diagnosis of HER2-targeted therapy-related cardiac dysfunction.	LVEF<50% prior to HER2-targeted therapy initiation or on completion of anthracycline treatment.
Cardiac function has ‘recovered’. ‘Recovery’ is defined as absence of heart failure symptoms with left ventricular ejection fraction (LVEF) increased to >50% for 6 months and N-terminal pro-B-type natriuretic peptide<125 ng/L.	Other ongoing guideline recommended indications for ACE inhibitors/angiotensin receptor blockers and/or beta-blockers.
Currently taking heart failure medications (at least any ACE inhibitor/angiotensin receptor blockers and/or beta-blocker).	Absolute contraindications to cardiovascular magnetic resonance.

HER-SAFERandomised Controlled Trial for the Safety of Withdrawal of Pharmacological Treatment for Recovered HER2 Targeted Therapy Related Cardiac Dysfunction

Exclusion criteria include ongoing cancer treatment for metastatic disease, life expectancy less than 12 months or another guideline-recommended indication to continue their specific HFT (including type 2 diabetes mellitus with hypertension who would be recommended to continue an ACE inhibitor/ARB regardless).^34^ Those with anthracycline CTRCD or other cardiomyopathies are also excluded—though patients may have received anthracyclines in their cancer treatment.

Participants will be recruited from local secondary care cardio-oncology and breast cancer services. Following approach by the study team potential participants will receive a copy of the participant information sheet and written informed consent (online supplemental material) will be obtained prior to any study visits.

### Randomisation procedure

Eligible participants will be randomised by a minimisation technique in favour of the arm that minimises imbalance between groups. This is conducted via dedicated peer reviewed open-source software,^35^ using a biased coin probability method (70%) and marginal balance distance method. Minimisation factors are: current age over 65 years, HFA-ICOS baseline cardiotoxicity risk stratification for HER2-targeted cancer therapies greater than low,^25^ CTRCD severity greater than mild,^36^ cumulative anthracycline dose greater than 250 mg/m^2^ and any radiotherapy to the left breast. This represents factors identifying those at the highest future CV risk at end of cancer treatment assessment.^33^

### Study schedule

The study schedule (online supplemental table 1) summarises procedures to be performed at each visit. Participants will undergo baseline assessment, randomisation to the controlled or experimental group and then follow-up over 12 months. At baseline, participants will undergo a comprehensive CMR with parametric mapping (T1, T2, extracellular volume) and contrast administration for early and late gadolinium enhancement imaging, to exclude patients with other causes of the prior cardiomyopathy including prior infarction.

Patients will undergo clinical assessment, ECG, cardiac biomarker testing (NTPro-BNP and high-sensitivity troponin; Roche platform electrochemiluminescence assays) and will complete heart failure QoL questionnaires (Kansas City Cardiomyopathy and Minnesota Living with Heart Failure), plus a medication disutility questionnaire (online supplemental material).

Follow-up visits will be at 6 and 12 months and participants will undergo a ‘rapid’ non-contrast CMR (including T1 and T2 parametric mapping), ECG, physical assessment, cardiac biomarker testing and complete heart failure QoL questionnaires.

At 6 weeks, 14 weeks and 9 months, participants will also have clinical assessment including symptoms, vital signs and cardiac biomarker testing.

Participants will be offered longer term follow-up outside the study period with subsequent data collection for 5 years, via annual clinical surveillance from the study sites cardio-oncology services.

### Phased medication withdrawal

Participants in the intervention arm will undergo phased withdrawal of heart failure medications according to a prespecified algorithm based on published algorithms.^22^ This had been designed following extensive consultation with independent experts and attempts to mimic ‘real-world’ medication withdrawal in clinical practice. Medications will be down titrated in a phased process every 2 weeks over a maximum of 16 weeks. Drug doses will be reduced by 50% in a stepwise manner every 2 weeks, until the patient is taking 25% or less of the maximum recommended dose at which point the medication will be stopped—before moving on to the next medication (figure 3). The controlled group will remain on their current HFTs.

**Figure 3 F3:**
[figure not shown]
Phased withdrawal of heart failure medications—medications are stopped sequentially and, in a step, wise approach.

### Sample size calculation

TRED-HF^22^ recruited 51 participants with 25 randomised to treatment withdrawal, 26 to treatment continuation. ‘Relapse’ outcome events occurred in 11/25 withdrawal patients within 6 months, with 0/25 outcomes in the continuation participants. Our retrospective pilot data (using local cardio-oncology service records) demonstrated 0/35 and 0/12 ‘relapse’ outcomes in study eligible patients who continued HFT compared with those who withdrew respectively (median 6 months of follow-up, IQR 6–10). Following discussion with patients from our pilot dataset, a 10% relapse rate following HFT withdrawal was considered acceptable, provided participants are under close surveillance. Using a binary outcome (‘relapse’ vs ‘no relapse’) non-inferiority design with α=0.05 (one sided) and 80% power, 74 participants (37 per study arm) are required to exclude a difference in favour of the controlled group of more than 10 percentage points. Assuming a 10% dropout rate, a sample size of n=90 is therefore considered sufficient.

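### The 80% power claimed for 37 per arm comes without an assumed relapse rate, and at the roughly 3% that reproduces 37 by the usual formula, exact power is well below 80%

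*Protocol article*

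**What the plan says.** The Sample size calculation section of the protocol article specifies a binary relapse outcome and a "non-inferiority design with α=0.05 (one sided) and 80% power", and concludes that "74 participants (37 per study arm) are required to exclude a difference in favour of the controlled group of more than 10 percentage points". The Recruitment row of Table 1 repeats this as "Target: 90 participants. Power: 74 participants". The section ends: "Assuming a 10% dropout rate, a sample size of n=90 is therefore considered sufficient".

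Three sets of rates stand beside the calculation, and none is identified as the design assumption:

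- The external withdrawal trial in recovered dilated cardiomyopathy: "11/25 withdrawal patients within 6 months, with 0/25 outcomes in the continuation participants".
- The local retrospective pilot: "Our retrospective pilot data (using local cardio-oncology service records) demonstrated 0/35 and 0/12" relapses in patients who continued and withdrew treatment respectively, at a median of 6 months.
- A 10% relapse rate after withdrawal, which patients from the pilot dataset considered acceptable.

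The Data analysis plan tests non-inferiority with a confidence interval for the absolute difference and does not name the type of interval. Under Endpoints, the primary outcome is counted over 12 months.

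**The concern.** A sample size for a risk difference depends on the event rate assumed in each arm. With none stated, 74 cannot be verified. The rate that most naturally reproduces 37 per arm is so low that the formula behind it is unreliable.

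At stake is how the result will be read. At 37 or 40 per arm, a score interval fails to show non-inferiority if one withdrawn patient relapses and no continuing patient does. A reader told that the trial had 80% power could take such a result as evidence against withdrawal, when the design makes it likely even if true relapse after withdrawal is as low as 3%.

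**Working it through.** **Inputs from the document.** One-sided alpha 0.05, power 80%, margin 10 percentage points, 37 per arm, 10% dropout, target 90 (all from Sample size calculation). **Assumptions made here.** The relapse rates and the interval type, because the article states neither.

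**1. Reproducing 37 per arm.** The unpooled normal approximation is

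n per arm = (1.645 + 0.842)² × [pc(1−pc) + pt(1−pt)] / [0.10 − (pt − pc)]²

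with pc the continuation rate and pt the withdrawal rate. The squared term is about 6.18.

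| Continuation v withdrawal | n per arm |
|---|---|
| 0% v 3% | 6.18 × 0.0291 / 0.0049 = 36.7 |
| 3% v 3% | 6.18 × 0.0582 / 0.01 = 36.0 |
| 3.09% v 3.09% | 37 |
| 5% v 5% | 58.7 |
| 10% v 10% | 111.3 |

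So the stated figure is reproduced at about 3%. The formula's own power at 37 per arm is 80.3% (0% v 3%) and 81.0% (3% v 3%). The observed pilot rates cannot be used in it: at 0% v 0% the variance is zero and it returns n = 0.

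**2. Why the approximation fails there.** The expected number of relapses in an arm at 3% is 37 × 0.03 = 1.1. Consider the outcome of one relapse after withdrawal and none on continuation, when the true rates are 0% v 10%:

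- P(0 of 37) = 0.9^37 = 2.0%
- P(1 of 37) = 37 × 0.1 × 0.9^36 = 8.3%
- P(at most 1) = 10.4%

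A test that declares non-inferiority at 1 v 0 therefore exceeds 5% error. One that does not can succeed at 0% v 3% only if no withdrawn patient relapses, so its power there is at most 0.97^37 = 32.4%.

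**3. Exact power.** This sums binomial probabilities over all outcomes at which the upper limit of the 90% two-sided interval lies below 10 points.

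| Per arm | Interval | Power, 0% v 3% | Power, 3% v 3% | One-sided error, 0% v 10% |
|---|---|---|---|---|
| 37 | Score (Miettinen-Nurminen) | 32% | 60% | 2.0% |
| 37 | Wald | 70% | 76% | 10.4% |
| 40 | Score | 30% | 63% | 1.5% |
| 40 | Wald | 66% | 83% | 8.1% |
| 45 | Score | 61% | 72% | 5.2% |
| 45 | Wald | 85% | 87% | 15.9% |

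At 37 per arm, Newcombe limits and a score-ordered exact unconditional test give the same 32% and 60%. Forty per arm is the recruitment target less 10% (90 × 0.9 = 81). Forty-five per arm is the full target with no loss. The rise in score power at 0% v 3% from 30% to 61% reflects discreteness: at 45 per arm the score interval first accepts 1 v 0, and its error there is slightly above 5%.

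**4. Where 80% does hold at 37 per arm.** Score power for equal rates in both arms is 100% at 0%, 85.7% at 0.5%, 80.0% at 0.8%, 77.0% at 1%, 66.7% at 2%, 59.7% at 3% and 49.6% at 5%. With no relapse on continuation, 80% requires (1 − p)^37 ≥ 0.80, so p ≤ 0.6%. Wald power reaches 80% up to about 2.6% in both arms, or 2.2% v 0%, but without holding the stated alpha.

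**5. What the pilot supports.** For 0 relapses in 12 withdrawn patients, the one-sided 95% upper limit is 1 − 0.05^(1/12) = 22%. Median follow-up was 6 months, against a 12-month endpoint.

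**6. Dropout.** 74 / 0.9 = 82.2, so 83 participants (84 for equal arms). Ninety covers a loss of 1 − 74/90 = 17.8%.

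**The case against.** The strongest reply is that 3% is not in the document. It is back-solved from one formula, and power is then judged by another method. A different starting point is possible: the Farrington-Manning formula gives 34.7 per arm at 0.5% in both arms and 40.4 at 1%, so 37 falls at roughly 0.7%, where a score interval does deliver about 80%. The pilot saw no relapse in 47 patients, and if nobody relapses power is 100%. This stands. A reader might infer that 80% can be reached only through a 3% rate and a normal approximation, or that the trial simply has 32% or 60% power. The document supports neither reading: those two figures are conditional on 0% v 3% and 3% v 3%.

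The article also condenses a full protocol that may give the rates and formula, and the interval may be fixed in an analysis plan. That excuses some silence, but it does not make the printed 80% true at rates near 3% once alpha is held.

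The Discussion describes the trial as a pilot of early outcomes that needs larger confirmation. This tempers how a failed result might be read. The objectives and Table 1 nevertheless present a powered non-inferiority comparison.

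On dropout, a reader might take the mismatch between 83 and 90 as an error that harms the trial. It does not: 90 is more than enough for 10% loss. Nor is 10% relapse in both arms a fair test of the authors' figure, since they offer 10% as acceptable after withdrawal and not as an expected rate.

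**Conclusion.** The point holds in conditional form. The article states 80% power without the relapse rates on which it depends. At the rates that reproduce 37 per arm by the usual formula, exact power is 32% (0% v 3%) or 60% (3% v 3%) with a score interval. Even a Wald interval, which does not hold alpha, reaches only 70% or 76%. Recruiting 90 helps only partly: score power is 30% or 63% at 40 per arm, and 61% or 72% at 45 per arm, the latter with 5.2% error at 0% v 10%.

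With a score interval, 80% at 37 per arm requires relapse of about 0.8% or less in both arms, or 0.6% or less v 0%. Such rates are possible, but they are not stated and a 0/12 pilot does not establish them. The conclusion assumes 1:1 allocation, a 90% two-sided interval and independent binomial outcomes. The dropout sentence is a minor matter of conservative rounding.

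**What to change.** In the Sample size calculation section and the Recruitment row of Table 1:

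- State the relapse rate assumed in each arm and the interval method to be used for the primary comparison.
- Replace the unqualified 80% with the exact power of that interval at about 40 and 45 per arm, over a grid of continuation v withdrawal rates (0/0, 1/1, 0/3, 3/3 and 5/5%).
- State the relapse rate up to which 80% power holds.
- Reword the dropout sentence: 10% loss needs 83 participants (84 for equal arms), and 90 covers about 18%.

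The cost is a rewritten paragraph and table row, and a less favourable stated power. No extra enrolment is proposed.
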